#### **4.3.3 Serology**

In order to carry out serological testing for SARS-CoV-2 antibodies, finger-prick testing to obtain a few drops of blood from all participants (children, childcare workers) will be used once at the beginning of the study programme and once more at the end of the study. The finger-prick tests will be carried out by trained staff supervised by pediatricians.

Venous blood samples will be taken only in the event of a positive or borderline result in the finger-prick test and only if explicit informed consent for venous blood sampling was obtained (cf. 4.2).

The serological tests will be carried out on site using a point-of-care test and at the Institute of Hygiene and Microbiology and/or the Institute of Virology at the University of Würzburg.

Any sample material remaining after carrying out the tests will be stored for a period of 10 years. Antibody tests for the detection of SARS-CoV-2 antibodies are at present being refined at a high rate of innovation. Storing any remaining sample material will enable renewed testing using more refined techniques in the future.

All study participants (parents/guardians in the case of children) will be notified of the serological test results. No respiratory sample collection and no further blood sampling at the end of the study will be performed in participating children and childcare workers tested positive in the initial serological test.

## 5 PARTICIPANT SAFETY

All oropharyngeal swabs and blood tests will be taken by medically trained staff who would be able to initiate emergency treatment in the extremely rare event of complications.

The saliva samples and, where applicable, mid-turbinate swabs that can be taken by the parents themselves after receiving practical instructions from the study team are in general to be carried out on the scheduled sampling days before bringing the child to the daycare centre. Before performing sample collection for the first time, parents will receive detailed explanations in the daycare centre. On the first sampling day, sample collection will be carried out within the premises of the daycare centre and will be supervised by medically trained staff. Parents will be provided with written instructions, including an emergency telephone number. In case parents are unable or unwilling to take the mid-turbinate swabs themselves, medical staff will be present in the daycare centre on sampling days.

## 6 DATA MANAGEMENT

### 6.1 Source data and source material

Data for the study will be obtained from participant lists, from paper based and electronic questionnaires and from sampling material.

#### **Recruitment/ individual course of study**

##### *Initial measurement*

The central study office will provide all participating daycare centers with the information material relevant to the assigned study module, the written participant documents (informed consent forms, initial questionnaire) and sealable envelopes pre-addressed to the central study office to be used by the parents/guardians to return the documents.

The participating daycare centers will collect the envelopes with the informed consent forms and the initial questionnaires returned by the parents/guardians and forward all documents to the study team. The central study office will check and archive the documents, create participant lists per daycare centre and assign a unique participant number to each participant (pseudonymisation).

The data pertaining to the study (initial questionnaire and follow-up questionnaires) will be stored in pseudonymised form in the EDC (Electronic Data Capture) system REDCap®.

The EDC system will be hosted on servers belonging to the University of Würzburg and administered by the University of Würzburg's computing centre. The security policy conforms to the University of Würzburg standard. Access to the stored data will be granted via the EDC system's role and rights management system.

##### *Follow-up questionnaires after 1, 6 and 12 weeks*

In preparation for the follow-up questionnaires at three pre-defined follow-up times (1, 6 and 12 weeks) implemented in the EDC system REDCap®, participants will be asked to provide their e-mail address in the informed consent form for participation in the study. Participants who provide a valid e-mail address will receive their personal access data (pseudonym and password) by e-mail. With this access data, they can verify their access to the EDC system and subsequently fill in the follow-up questionnaire using eCRF.

Parents will be provided with pre-labelled test tubes and other material for the mid-turbinate swabs and saliva samples taken at home. The test tubes handed in by the parents at the daycare centre will be collected by members of the study team and taken to the diagnostic laboratory.

All other mid-turbinate swabs as well as all oropharyngeal swabs and blood samples will be carried out by medically trained staff, labelled and documented, and the samples will be forwarded to the diagnostic laboratory at the Institute of Hygiene and Microbiology or the Institute of Virology at the University of Würzburg for analysis.

The laboratory samples will be labelled with the name and date of birth of the participant in order to allow for the necessary timely notification of both the participant (parents/guardians) and the local health authorities in the event of a positive test result for SARS-CoV-2.

In addition, the study team members on site at the child care centers will document the attendance status of participating children (present / planned absence (e.g. holiday) / unexpected absence (e.g. due to illness with/without respiratory/gastrointestinal symptoms) and the status regarding successful sample collection (mid-turbinate swab or saliva sample). This documentation will be forwarded to the central study office.

Children aged three years and above will be interviewed within the daycare centre after 2, 6 and 12 weeks by members of the study team using a paper-based questionnaire. The data will be pseudonymised in the central study office, entered into the RedCap database and forwarded to the Institute for Clinical Epidemiology and Biometry for analysis.

Data on the acceptance of the measures by parents and by the staff at the daycare centre will be gathered both with quantitative methods using questionnaires for all participants and with qualitative methods using semi-structured guideline interviews in all groups of participants (after obtaining separate informed consent). The interviews will be carried out by members of the Department for General Medicine in cooperation with the Department of Child and Adolescent Psychiatry, Psychosomatics and Psychotherapy.

In addition, questionnaires will be used to gather basic data on characteristics of the daycare centers (group sizes, number of childcare workers per group) and infection data at the level of the daycare centers (number of cases per participant (child/childcare worker) at the centre). The questionnaires will be sent to the central study office and the data will be forwarded to the Institute for Clinical Epidemiology and Biometry for analysis.

Data on the number of absent days per daycare centre and week will be documented in anonymous form per group by the staff at the daycare centre, sent to the central study office and forwarded to the Institute for Clinical Epidemiology and Biometry for analysis.

On sampling days, the number of staff and the time required for sample collection and documentation will be recorded both for study team members and for staff of the daycare centre. In order to determine the material costs and testing costs, the number and type of samples collected will also be recorded. If sampling is performed at home by the parents, they will be asked to document the time required for sample collection and labelling.

## 6.2 Study database

Management of participant documents will be performed centrally at the central study office. Only pseudonymised data will be recorded (central study office at the Institute of Hygiene and Microbiology, electronic questionnaires at the Institute of Epidemiology and Biometry).

Sample material will be analysed at the Institute of Hygiene and Microbiology and the Institute of Virology and the results will be entered in Excel databases. The results will be transferred to the central study office using a password protected exchange directory restricted to this study and will be forwarded to the Institute for Clinical Epidemiology and Biometry in pseudonymised form for analysis.

For further analyses, the Institute for Epidemiology and Biometry will merge the data gathered in the questionnaires with the laboratory results in pseudonymised form using the participant number.

All data obtained in the process of the study and for analysis purposes will be stored in two separate systems. Every participant will be assigned a unique participant number (pseudonym) and all questionnaires and interviews will use only this pseudonym and no information relating to an identified natural person. The research data can be linked with the information relating to an identified natural person by the de-identification list in conjunction with the pseudonym. During the process of data linkage, the research data will be classed as “information relating to an identifiable natural person” and the applicable data protection regulations will be binding. For these purposes, the central data processing unit (Institute for Clinical Epidemiology and Biometry / ICE-B) will programme a separate data base for the storage of contact details, e-mail addresses and the respective pseudonyms.

## **6.3 Laboratory methods**

### **6.3.1 Virus detection**

Polymerase chain reaction (PCR)

### **6.3.2 Antibody detection**

Enzyme-linked immunosorbent assay (ELISA), point of care test (lateral-flow ELISA)

## **6.4 Sampling**

### **6.4.1 Mid-turbinate swabs**

Mid-turbinate swabs will be performed as mid-turbinate swabs, to be carried out by tilting the child's head back slightly, inserting the swab frontally into a nostril and rotating the swab three times.

### **6.4.2 Saliva samples**

The parents will be provided with pre-labelled test tubes (50 ml) for taking saliva samples. The test tubes will either be filled directly with saliva or by using the following procedure: After filling the test tube with 10ml of still water or tap water, the parents let the child rinse their mouth with the solution and spit it back into the test tube.

### **6.4.3 Blood tests**

Blood samples will be taken using finger-prick testing with single-use safety lancets. After disinfecting and pricking the fingertip, a few drops of blood will be drawn into a capillary tube for performing the point of care test.

In the event of a positive or borderline result (approximately 1% of test results), parents/guardians will be given the option of additional venous blood sampling (1ml, in accordance with WHO guidelines ), which will be carried out by a physician under the supervision of a pediatrician if written consent is obtained.

## 7 BIOMETRICAL ASPECTS

### 7.1 Endpoints

#### Primary endpoints for the different surveillance measures

- [Modules 1-3]: Rate of acceptance of the respective surveillance protocol defined as: proportion of children/childcare workers with “successful” participation in sample collection (mid-turbinate swab or saliva sample) among all children and childcare workers in the daycare centre. Parent/child groups and childcare workers who do not consent to participation in the study will be included in the calculations as “non-successful” participants. Each study participant will be classed as “successful” with respect to sample collection if at least 60% of all scheduled samples were collected successfully.

A surveillance protocol will be classed as “successful” if the rate of acceptance exceeds the following level:

≥30% (Module 1: intensive monitoring / mid-turbinate swabs)

≥37.5% (Module 2: extensive monitoring / mid-turbinate swabs)

≥37.5% (Module 3: intensive monitoring / saliva samples)

- [Module 4]:  
Proportion of cases with successful sample collection (i.e. completion of sample collection and diagnostic analysis – or receipt of test result in the case of external testing – within 72h after first telephone contact with hotline) among all cases of sample collection recommended for symptomatic children, symptomatic childcare workers or symptomatic household members of children/childcare workers

The surveillance protocol will be classed as “successful” if the rate of acceptance exceeds the following level:

≥70% (Module 4: symptom-based monitoring)

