|  | 
children/childcare workers with “successful” participation in sample collection (mid-turbinate swab or saliva sample) among all asymptomatic children and childcare workers in the daycare centre.
 
Asymptomatic is in this case defined as: absence of respiratory symptoms that would lead to the child / childcare worker being excluded from attending the daycare centre according to the hygiene measures in place at the time of the scheduled sample collection.
 
Parent/child groups and childcare workers who do not consent to participation in the study will be included in the calculations as “non-successful” participants. Each study participant will be classed as “successful” with respect to sample collection if at least 60% of all scheduled samples were collected successfully.
 
A surveillance protocol will be classed as “successful” if the rate of acceptance exceeds the following level:
 
≥30% (Module 1: intensive monitoring / mid-turbinate swabs)
 
≥37.5% (Module 2: extensive monitoring / mid-turbinate swabs)
 
≥37.5% (Module 3: intensive monitoring / saliva samples)
 
 
• [Module 4]: Rate of acceptance of the surveillance measure:
 
 
Proportion of cases with successful sample collection (i.e. completion of sample collection and diagnostic analysis – or receipt of test result in the case of external testing – within 72h after first telephone contact with hotline) among all cases of sample collection recommended for symptomatic children, symptomatic childcare workers or symptomatic household members of children/childcare workers
 
The surveillance protocol will be classed as “successful” if the rate of acceptance exceeds the following level:
 
≥70% (Module 4: symptom-based monitoring)
 
Secondary endpoints (inter alia):
 
 
• Acceptance of mid-turbinate swab sample collection (proportion of successfully completed swabs), acceptance of saliva sampling (proportion of successfully performed sampling), acceptance of blood sampling (proportion of blood samples performed in relation to all scheduled blood samples)
 
• Satisfaction and sense of security of families/children (using questionnaires and validated scores)
 
 |

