#### **3.3 Exclusion criteria for participants in the daycare centers**

- Missing written consent
- Module 3: Children aged  $<2$  years at the time of the start of the study

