#### **4.3.1 Monitoring programmes (SARS-COV-2)**

##### **4.3.1.1 Module 1: Intensive Monitoring – mid-turbinate swabs (1 centre, at least 100 children,**

2 mid-turbinate swabs per week)

All participating children and childcare workers in the selected daycare centre will be tested for SARS-CoV-2 with a mid-turbinate swab (cf. 6.4.1) twice a week (on Mondays and Thursdays). Test results will be available 24 hours after taking the swab. If a person is tested positive for SARS-CoV-2, the case module (4.3.1.8) will come into effect.

The monitoring programme will be continued for a period of 12 weeks.

4.3.1.2 Module 2: Extensive Monitoring – mid-turbinate swabs (1 centre, at least 100 children, 1 mid-turbinate swab per week)

All participating children and childcare workers in the selected daycare centre will be tested for SARS-CoV-2 with a mid-turbinate swab (cf. 6.4.1) once a week (on Wednesdays). Test results will be available 24 hours after taking the swab. If a person is tested positive for SARS-CoV-2, the case module (4.3.1.8) will come into effect.

The monitoring programme will be continued for a period of 12 weeks.

4.3.1.3 Module 3: Intensive Monitoring – saliva samples (1-3 centers, at least 175 children overall, 2 saliva samples per week)

All participating children and childcare workers in the selected daycare centers will be tested for SARS-CoV-2 using a saliva sample (cf. 6.4.2.) twice a week (on Tuesdays and Fridays). Test results will be available 24 hours after sampling. If a person is tested positive for SARS-CoV-2, the case module (4.3.1.8) will come into effect.

Children below the age of 2 years will not be included in the monitoring programme of module 3.

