### **7.3 Populations for analysis**

The main analysis will include the data of all participants.

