### **7.5 Sample size discussion and power analysis**

Due to the study design as a feasibility study, the primary endpoint for modules 1-3 is the rate of acceptance of the respective surveillance protocol, defined as the proportion of children and childcare workers with successful participation in sample collection (mid-turbinate swab or saliva sample) among all children and childcare workers in the daycare centre. Parent/child groups and childcare workers who do not consent to participation in the study will be included in the calculations as “non-successful” participants. Each study participant will be classed as “successful” with respect to sampling if at least 60% of all scheduled samples were collected successfully. All persons with a positive serological test for SARS-CoV-2 will be classed as “successful” with regard to the primary endpoint as no further sample collection (mid-turbinate swabs or saliva samples) is to be carried out in these cases according to the surveillance protocol.

As the maximum achievable sample size will depend on the number of children and number of childcare workers per centre, it is only possible to state a minimum sample size per module. The estimates of precision will be based on this minimum sample size. If the sample size is greater than expected, the width of the precision estimate will be reduced, allowing a more precise estimation.

The inclusion criteria result in the following minimum sample sizes (number of children and childcare workers) per module:

Module 1 (intensive monitoring / mid-turbinate swabs): 105

Module 2 (extensive monitoring / mid-turbinate swabs): 105

Module 3 (intensive monitoring / saliva samples): 185

Module 4: 275

We assume that the rate of acceptance will depend on the frequency of sampling and the type of sample collection. Based on this assumption, we expect a lower rate of acceptance in module 1 (mid-turbinate swabs twice a week) than in module 2 or 3. We therefore assume the following rates of acceptance:

Module 1 (intensive monitoring / mid-turbinate swabs): 30%

Module 2 (extensive monitoring / mid-turbinate swabs): 37.5%

Module 3 (intensive monitoring / saliva samples): 37.5%

Reasoning for sample size in module 1 (intensive monitoring / mid-turbinate swabs):

A minimum number of 100 children and 5 childcare workers is sufficient to estimate a rate of acceptance of 30% with a precision (half the width of the 95%-CI using the Wilson score method) of max. 9.1%.

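### The synopsis and section 7.1 give different denominators for the Modules 1-3 acceptance rate, and 7.1 read literally counts Module 3's excluded under-2s as non-successes

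*Protocol*

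**What the plan says.** The primary endpoint for Modules 1-3 is a proportion of persons. It is defined in three places in the protocol.

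- **Synopsis (1.4):** the denominator is persons successful "among all asymptomatic children and childcare workers in the daycare centre". Being asymptomatic means having no respiratory symptoms that would bar attendance "according to the hygiene measures in place at the time of the scheduled sample collection".
- **7.1 and 7.5:** the denominator is "among all children and childcare workers in the daycare centre", with no limit by symptoms or age.
- **All three:** people who do not consent are counted as non-successful, and a participant is successful "if at least 60% of all scheduled samples were collected successfully".

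Four other places bear on who is counted.

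- **Module 3 eligibility:** 3.3 excludes children under 2 at study start, and 4.3.1.3 says "Children below the age of 2 years will not be included in the monitoring programme of module 3".
- **Planned size:** 7.5 gives "Module 3 (intensive monitoring / saliva samples): 185". This is 175 children plus 10 workers, and the synopsis and 3.1 restrict the 175 to children aged 2 years or older.
- **Seropositive persons:** 4.3.3 stops respiratory sampling for those positive at the first serological test. Only 7.5 says that seropositive persons count as successful.
- **Analysis population:** 7.3 says "The main analysis will include the data of all participants", while 3.3 lists "Missing written consent" as an exclusion.

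The acceptance criteria are 30% (Module 1) and 37.5% (Modules 2 and 3). Section 1.6 makes planning of the subsequent study conditional on at least one programme meeting its criterion.

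**The concern.** The synopsis and 7.1 differ by one word that changes who is divided by. The synopsis version cannot be computed as it stands: a person is asymptomatic on some sampling days and not on others, whereas success is one verdict per person over 12 weeks. The condition makes sense only as part of deciding which samples were scheduled for a person, and neither text puts it there.

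The 7.1 version has a different problem. A Module 3 centre may well have children under 2: the study population starts at age 1, and 3.1 asks for a minimum number of older children rather than for no younger ones. If all children in the centre are counted, these children enter the denominator although the protocol bars them from sampling. The Module 3 rate then measures the age mix of the centre as well as acceptance. Modules 1 and 2 carry no such dilution, yet 7.1 and 7.2 compare acceptance across Modules 1-3.

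At stake are the success classification of each protocol and the comparison between modules.

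**Working it through.** **1. The plan's own figure.** Section 7.5 states a precision of at most 6.9% for Module 3. The half-width of the Wilson 95% interval is z·√(p(1−p)/n + z²/(4n²)) / (1 + z²/n). With p = 0.375, n = 175 + 10 = 185 and z = 1.96 it is 0.0691. The stated figure is reproduced, so Module 3 was sized on eligible persons only.

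**2. Module 3 with and without under-2s.** The fewest successes that meet the criterion on 185 is 70, because 0.375 × 185 = 69.4.

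- Eligible persons only: 70/185 = 37.8%, pass.
- One under-2 added: 70/186 = 37.6%, pass.
- Two under-2s added: 70/187 = 37.4%, fail.

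The share of under-2s is not stated, so a range is assumed. If they are a share s of all children in the Module 3 centres, there are u = 175·s/(1−s) of them. The literal rate is 70/(185 + u). The number of successes needed is 0.375·(185 + u), rounded up.

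| s (assumed) | u | Rate with 70 successes | Successes needed | Needed rate among the 185 |
|---|---|---|---|---|
| 5% | 9.2 | 36.0% | 73 | 39.5% |
| 10% | 19.4 | 34.2% | 77 | 41.6% |
| 20% | 43.8 | 30.6% | 86 | 46.5% |
| 30% | 75.0 | 26.9% | 98 | 53.0% |

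**3. Synopsis wording against 7.1.** If the synopsis wording removed two persons from the denominator:

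- Module 1: 31/105 = 29.5% fails, 31/103 = 30.1% passes.
- Module 3: 69/185 = 37.3% fails, 69/183 = 37.7% passes.

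**4. What counts as scheduled.** Twice-weekly sampling for 12 weeks gives 24 samples, so 60% is 14.4 and 15 are needed; 9 may be missed. Weekly sampling gives 12, so 7.2 and 8 are needed; 4 may be missed. If 6 of 24 days fall in periods of exclusion for symptoms, the need is 15 of the 18 remaining days when those days count as scheduled. It is 11 of 18 when they do not (0.6 × 18 = 10.8).

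The effect depends on assumptions that the protocol does not supply. Take a child who gives a sample on 80% of available days, independently, with no sample taken on lost days:

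- 2 of 24 days lost: probability of success 0.94 if they count as scheduled, 0.98 if they do not.
- 6 of 24 days lost: 0.50 against 0.98.

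**The case against.** Several points can fairly be said for the plan.

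**Section 7.3 is not a third denominator.** A reader might infer from 7.3 and 3.3 that the primary rate is computed among consenters only, which would raise it sharply. The documents do not support this. The synopsis, 7.1 and 7.5 all expressly count non-consenters as non-successful, and 7.1 even uses the word participants for them. A one-line general sentence does not override a rule stated three times. It is loose wording, since 4.2 calls the same people non-participants.

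**Ill children are not classed as refusers.** A reader might infer that too. Under 7.1 a child who was ill stays in the denominator and still succeeds with 60% of the scheduled samples. Section 4.3.1.5 lets parents sample symptomatic children themselves, so an illness day need not be a lost sample. Section 1.8 says symptomatic persons are not part of the Modules 1-3 surveillance, which favours leaving such days out of the schedule. The large contrast with 6 lost days is one assumed scenario.

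**The age limit is evident elsewhere.** The synopsis, 3.1, 3.3, 4.3.1.3 and 4.3.1.6 all restrict Module 3 to age 2 or older, and 7.5 says its minimum sizes follow from the inclusion criteria. The intended denominator is probably the eligible roll.

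**The decision is partly insulated.** Section 1.6 needs only one of four programmes to meet its criterion, Module 4 is unaffected, and 7.2 calls all analyses exploratory.

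These points limit the finding but do not remove it. The synopsis and 7.1 still disagree, and the sentence that defines the endpoint still omits the age limit. A detailed counting rule for missed samples can sit in a statistical analysis plan; two conflicting denominators for the primary endpoint in the protocol should not.

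**Conclusion.** The inconsistency is real and should be fixed. There are two conflicting wordings of the primary denominator, one of which cannot be applied to persons. The other, read literally, adds Module 3 children whom the protocol excludes and whom its own sample size leaves out.

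The size depends on the result. Near a threshold, two persons are enough to reverse the classification. Away from it, the verdict changes only if under-2s are numerous, and the 5% to 30% range used for that is an assumption. Results close to the cut-off are not a remote case, because 7.5 assumes acceptance rates equal to the success thresholds.

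Under-2s are near-certain rather than absolutely certain non-successes, since 7.5 classes any seropositive person as successful. Neither 7.1 nor the synopsis carries that rule.

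**What to change.** Use one definition in the synopsis, 7.1 and 7.5:

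- **Persons:** all eligible children (Module 3: aged 2 years or older at start) and childcare workers on the centre's roll at module start. Those who do not consent count as non-successful.
- **Seropositive persons:** carry the 7.5 rule into 7.1 and the synopsis. Without it, a consenting person whose sampling stops after a positive first test would fall short of 60%.
- **Scheduled samples:** take the symptom condition out of the denominator and put it into the 60% rule, so that a sample is scheduled only on days when the person was not excluded from attendance for symptoms. Report a sensitivity analysis that counts all sampling days.
- **7.3:** state that the primary analysis for Modules 1-3 includes non-consenters.
- **Comparison of modules:** compare Module 3 with Modules 1 and 2 also in children aged 2 years or older.

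The cost is mainly wording, and the change should be settled before any data are seen. One addition to data collection is needed: 6.1 provides for recording attendance status and reason for absence for participating children, so the same must be logged for childcare workers.
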